### Reference standard

The reference standard is histology where endometrial tissue is collected for routine diagnostic and staging purposes. The hysterectomy specimen will be used in preference to the endometrial biopsy, where available within 3 months of endometrial biopsy and where there was no treatment with neoadjuvant chemotherapy or hormone therapy. Histology results will be classified as inadequate, benign, atypical hyperplasia and endometrial cancer (of any histological subtype or grade). For the primary analysis, a histological diagnosis of endometrial cancer will be considered a positive result. We will report overall results as well as a breakdown by histological subtype and stage of disease. Hyperplasia and benign endometrium will be considered a negative result. In secondary analyses, cancers of other pelvic sites (cervix, vagina, uterus, ovary, fallopian tube, bladder, kidney or bowel) will be considered a positive result. We will record cases of atypical hyperplasia and their cytological interpretation. In cases where an endometrial biopsy is not indicated (endometrial thickness <4 mm and/or normal hysteroscopy) or fails (inadequate sample), the reference standard will be discharge from diagnostic workup. Passive clinical follow-up of negative women will ensure missed diagnoses of endometrial cancer are minimised. This will involve monitoring for any subsequent rereferrals to our service. A diagnosis of endometrial cancer within 3 months of initial discharge from diagnostic workup will be considered a positive clinical result.

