Analysis of the primary objective will compare the clinical performance of cytology with the reference test. Thus, sensitivity, specificity, NPV, positive predictive value and diagnostic accuracy will be reported together with their corresponding 95% CIs, calculated using the exact binomial method. Where a histology result is not available, endometrial thickness <4 mm (histology not indicated) or discharge from diagnostic workup will be used as reference standard. Analysis of the secondary objectives will assess clinical performance of the urine test alone and the vaginal test alone for the detection of endometrial cancer in relation to the reference test. The clinical performance of urine and vaginal cytology for the detection of any cancer affecting the pelvic organs will also be calculated. Secondary analyses will follow the same approach as the primary analysis. Sensitivity analyses will consider the clinical performance of cytology with a broader definition of a positive cytology result (including glandular results as test positives). Interobserver agreement between the cytopathologists will be assessed using the kappa statistic and categorised as poor, fair, moderate and good. McNemar’s χ^2^ test will be used to compare urogenital cytology with routine diagnostics. Multivariate logistic regression will evaluate the relationship between positive cytology and endometrial cancer diagnosis while adjusting for potentially predictive clinical characteristics like age and BMI. The diagnostic accuracy of urogenital cytology will be compared with individual elements of the standard diagnostic pathway, including TVS, hysteroscopy and endometrial biopsy. Consideration will be given as to where in the current diagnostic pathway for endometrial cancer urogenital cytology fits. Its use as a triage test prior to any other diagnostic workup both alone and in combination with clinical parameters (eg, age and BMI) will be modelled. We will also consider its usefulness in combination with transvaginal ultrasound scanning at various endometrial thickness cut-offs. The acceptability of urogenital sampling will be compared with transvaginal ultrasound, hysteroscopy and endometrial biopsy (online supplemental appendix 1).

10.1136/bmjopen-2021-050755.supp1Supplementary data

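### The comparison of cytology with TVS, hysteroscopy and biopsy uses a reference standard that those tests help to define, which inflates biopsy accuracy, TVS sensitivity and, in part, hysteroscopy sensitivity

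*Protocol article*

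**What the plan says.** The Reference standard section starts from routine tissue: "The reference standard is histology where endometrial tissue is collected for routine diagnostic and staging purposes". One replacement is allowed: "The hysterectomy specimen will be used in preference to the endometrial biopsy, where available within 3 months of endometrial biopsy", provided that no neoadjuvant chemotherapy or hormone therapy was given. Where a biopsy is not indicated or fails, the section reads: "endometrial thickness <4 mm and/or normal hysteroscopy) or fails (inadequate sample), the reference standard will be discharge from diagnostic workup". The Statistical analyses section makes the ultrasound result itself a reference: "Where a histology result is not available, endometrial thickness <4 mm (histology not indicated) or discharge from diagnostic workup will be used as reference standard".

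The same Statistical analyses section plans three uses of the pathway tests as comparators:

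- Element by element: "The diagnostic accuracy of urogenital cytology will be compared with individual elements of the standard diagnostic pathway, including TVS, hysteroscopy and endometrial biopsy".
- By hypothesis test: McNemar's χ² "test will be used to compare urogenital cytology with routine diagnostics".
- In combination: "We will also consider its usefulness in combination with transvaginal ultrasound scanning at various endometrial thickness cut-offs".

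No other reference standard is named for any of these, and secondary analyses are said to take the same approach as the primary one.

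Three provisions can correct a wrong negative: the hysterectomy replacement; passive monitoring of re-referrals, which counts a cancer diagnosed within 3 months of discharge (Reference standard); and, when cytology is positive but the pathway is incomplete, a request that the clinician consider further tests (Handling of discordant results).

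**The concern.** A comparator that helps to decide who has the disease is judged partly against its own result. This is incorporation bias. Here it comes with differential verification, because a thick endometrium leads to tissue and a thin one usually does not. A cancer missed by a pathway test tends to drop out of that test's denominator. A cancer found by cytology but missed by the pathway is scored as a cytology false positive.

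The plan means to use these comparisons to say where cytology belongs in the pathway, including as triage before any other workup. A tilt in the comparison would carry into that conclusion.

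**Working it through.** **Inputs from the protocol.** About 2000 women, 5% prevalence, hence 100 with and 1900 without endometrial cancer; sensitivity 85% ± 7% (Sample size). These agree with each other: 1.96 × √(0.85 × 0.15 / 100) = 0.070. No stated figure is in dispute; 100 and 85% only set the scale below.

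**Step 1: what each comparator is judged against.**

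| Comparator | Missed cancer | False alarm |
|---|---|---|
| Biopsy | Scored negative unless hysterectomy or later diagnosis corrects it | Scored as cancer unless hysterectomy disagrees |
| TVS at 4 mm | No tissue: scored negative unless corrected later | Benign histology at ≥4 mm is a counted false positive |
| Hysteroscopy | Normal and no tissue: scored negative unless corrected later. With tissue: judged by histology | Suspicious lesion with benign histology is a counted false positive |

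So biopsy is protected on both measures, TVS on sensitivity, and hysteroscopy on sensitivity only where no tissue is taken.

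**Step 2: general size.** Let s be a comparator's true sensitivity and f the share of its missed cancers that the reference later picks up. Apparent sensitivity = s / (s + (1 − s)f). The document gives neither s nor f, so both are assumed:

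| True s | f = 0 | f = 0.1 | f = 0.25 | f = 0.5 | f = 1 |
|---|---|---|---|---|---|
| 85% | 100% | 98.3% | 95.8% | 91.9% | 85% |
| 90% | 100% | 98.9% | 97.3% | 94.7% | 90% |
| 95% | 100% | 99.5% | 98.7% | 97.4% | 95% |

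**Step 3: TVS against cytology.** Assume 105 true cancers, 5 of them below 4 mm. Cytology detects 85 of the 100 at or above 4 mm and 4 of the 5 below.

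- Truth: TVS 100/105 = 95.2%; cytology 89/105 = 84.8%; gap 11/105 = 10.5 points.
- If k of the 4 cytology-positive thin-endometrium cancers are uncovered and the fifth is not, TVS = 100/(100 + k), cytology = (85 + k)/(100 + k), and the gap = (15 − k)/(100 + k).

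| k | TVS | Cytology | Gap (points) |
|---|---|---|---|
| 0 | 100% | 85.0% | 15.0 |
| 2 | 98.0% | 85.3% | 12.7 |
| 4 | 96.2% | 85.6% | 10.6 |

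**Step 4: cytology's specificity.** If the pathway misses 5 to 15 cancers beyond the 100 (assumed) and cytology detects 85% of them, 0.85 × 5 = 4.25 to 0.85 × 15 = 12.75 correct positives become false positives. Specificity moves from 1615/1900 = 85.0% to 1615.75/1905 = 84.8% or 1617.25/1915 = 84.5%. This effect is small.

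**Step 5: McNemar's test.** If routine diagnostics means the reference itself, 85/100 against 100/100 gives discordant pairs of 15 and 0, exact p = 2 × 0.5¹⁵ = 0.00006. Among reference positives no discordant pair can favour cytology, so the test carries no comparative information.

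**Step 6: TVS specificity.** If 30% to 60% of women without cancer measure ≥4 mm (assumed), apparent TVS specificity is about 70% down to 40%.

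**Step 7: enrichment.** If the midpoint enrichment in the Blinding section is used, women recruited for thickness above 4 mm or for proven cancer are selected on a comparator's result, which adds to the dependence.

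**The case against.** A reader might infer that all three comparators are near-perfect by construction. The document does not support that. Women at or above 4 mm go to biopsy and suspicious lesions are biopsied (Clinical diagnostic pathway), so TVS and hysteroscopy both collect counted false positives. Histology also prevails over thickness wherever tissue exists.

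A reader might also take 15 points as the gap the study would report. That is the worst case. The request for further tests after positive cytology could uncover the thin-endometrium cancers that cytology finds, and with all 4 uncovered the reported gap is almost the true one. For the same reason it does not follow that cytology must appear to add nothing below 4 mm. Whether a woman below 4 mm counts as having an incomplete pathway depends on figure 2, which is not available here.

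Three further points are fair. The text does not say that cut-offs below 4 mm will be examined, and those above can be. The comparisons are not among the listed primary or secondary outcomes, and the section on planned secondary use places assessment of pathway elements outside the scope of the accuracy study. An unseen analysis plan could name a different reference or subset.

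These points limit size and severity but leave the defect in place. The article does fix a reference standard that includes the comparators, and it plans the comparisons without another. The correcting provisions are partial: monitoring is passive and counts 3 months, hysterectomy acts mainly in women who go to surgery, and the further-tests request only asks the clinician to consider them.

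**Conclusion.** The point holds in a limited form. As written, the plan compares biopsy largely with itself and biases TVS sensitivity, and part of hysteroscopy sensitivity, upward relative to cytology. The direction follows from the stated rules. The size does not, because it depends on true comparator sensitivity and on how many missed cancers are later found, and the document gives neither. The range of about 10.6 to 15 points against a true 10.5 rests wholly on the assumed counts in Step 3. The McNemar objection applies to the reading in which routine diagnostics is the reference itself; the wording does not settle this. TVS specificity is not made near-perfect. The secondary comparisons and the placement of cytology in the pathway are affected. The change should be made, but the primary design does not depend on it.

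**What to change.** Change the analysis wording only:

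- Drop the accuracy comparison of cytology with biopsy where biopsy is itself the reference, and run no McNemar test of cytology against the reference.
- Report TVS sensitivity at 4 mm as an upper bound.
- Restrict hysteroscopy comparisons to women with histology and label them conditional on verification, since women with a normal hysteroscopy and no tissue are left out.
- Evaluate thickness cut-offs only at 4 mm and above, with performance stated as relative to 4 mm.
- As a sensitivity analysis, also count endometrial cancers found by the March 2022 data cut. State that this reduces but does not remove the dependence on TVS, because histology is still triggered largely by thickness. State also that follow-up varies: with recruitment from September 2018 to September 2021 it runs from about 42 down to 6 months, so later counts may mix missed with newly arising cancers.

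No new tests or visits are needed. The cost is fewer headline comparisons.

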### Planned secondary use of the data and samples

Beyond the scope of this diagnostic accuracy study, we will use the prospectively collected data to assess the clinical performance of elements of the current diagnostic pathway, alone and in combination, including formal cost-effectiveness analyses, if resources permit. We will use the data to validate and compare the clinical performance of several published endometrial cancer risk prediction models and to develop a novel risk prediction model that includes urogenital cytology. We will report descriptive analyses of our cohort of women with PMB, including the distribution of risk factors and patterns of help-seeking behaviour. Residual urine and vaginal samples will be embedded in agar cell blocks or spun down and frozen for future translational research. Agar cell blocks will be used to identify cellular markers by immunohistochemistry that distinguish benign from malignant cells, for example, proliferation markers (Ki-67 and minichromosome maintenance (MCM) 2, which may facilitate their identification using adjunct immunocytochemistry, single-cell platforms or flow cytometry. Frozen cell pellets and supernatant fractions will be used to search for novel genomic, metabolomic and proteomic biomarkers.

### Ethics and dissemination

This study was adopted onto the National Institute for Health Research trial portfolio on 7 August 2018 and is sponsored by MFT. Any planned modifications to the protocol will be approved by the REC before they are adopted by the study. An audit trail of ethical amendments and documentation will be kept to allow monitoring by the research team and external regulatory bodies (table 2). The study was registered with an International Standard Randomised Controlled Trial Number on 9 August 2018.

**Table 2 T2:** Summary of ethical amendments

Protocol	Date	Summary of changes
V3	24.05.2018	Funding and approval secured to expand the study to allow multicentre recruitment and NIHR portfolio adoption
V4.1	15.10.2018	Additional exclusion criteria added: Mirena coil in situ or removed within the last 3 months. Any other condition that would compromise participant safety or data integrity.
V4.3	06.03.2020	Approval to allow recruitment strategy to include proven endometrial cancer cases prior to hysterectomy
V4.4	16.07.2020	Approval to allow remote consent and data collection, if required, as part of COVID-19 safety mitigation measures

NIHR, National Institute for Health Research.

### Study management

The study management group comprises the principal investigator, project manager, cytology team, clinical research fellows, research nurses and statistician, who will jointly monitor study conduct and progress. All aspects of the study and all study personnel will adhere to the study protocol (version 4.4 or subsequent approved version) and Good Clinical Practice and Data Protection principles. Regular team meetings will ensure quick resolution of recruitment issues, study processes and data collection inconsistencies.

### Patient and public involvement

The research question was developed in dialogue with patients, carers, members of the public and healthcare professionals. ‘Which women with abnormal bleeding require specialist referral for investigation?’ was ranked the second most important unanswered research question in the James Lind Alliance Womb Cancer Priority Setting Partnership, recognising the need for better diagnostic pathways for endometrial cancer.^19^ ‘What simple, non-invasive, painless, cost-effective and convenient tests can be used to detect cancer early?’ was voted the most important research priority for detecting cancer early.^8^ Urogenital cytology is simple, non-invasive and painless; whether it is effective for the detection of endometrial cancer is the focus of this study. We will disseminate our results through publication in peer-reviewed scientific journals; presentation at conferences; and via social media, blogs and charity websites.

## Discussion

The DETECT Study will establish the diagnostic test accuracy of vaginal and urine samples for endometrial cancer detection by cytology in women with PMB. Urogenital cytology could offer a simple, acceptable, easy to administer test that could be used in primary care as a triage tool for women with unexplained PMB. Cytology positive women could be referred for diagnostic workup, while cytology negative women are quickly reassured without the need for unpleasant, invasive, anxiety-provoking tests, with massive cost-saving implications for the NHS.
